# An integrated theory based-educational intervention to change intention to have a child: study protocol of a cluster randomized controlled trial

**DOI:** 10.1186/s12978-024-01760-x

**Published:** 2024-02-28

**Keywords:** Childbearing, Stages of change model, Theory of planned behavior, Training couple

## Abstract

**Background:**

In high- and low-income countries, declining birth rates have become a global concern. Couples do not have enough information about the complications of delaying and reducing childbearing and this leads them to make inappropriate decisions. Therefore, this study aims to evaluate whether an educational program based on integrating the Theory of Planned Behavior (TPB) and the Trans-Theoretical Model (TTM) affects child-free couples’ intention to have children and minimizes the consequences of this decline.

**Methods:**

Thirty couples (intervention, n = 15; control, n = 15) will be enrolled in this cluster randomized controlled trial. After collecting baseline data and separating participants in the pre-contemplation and contemplation stages based on the TTM, the samples were randomly assigned to the intervention and control groups. The intervention group will receive 60-min training based on TPB components for 4 weeks. The first follow-up assessment was performed immediately after the intervention and the final assessment 6 months later. For all 3 time assessments, three questionnaires will be used: The knowledge questionnaire, the TTM, and the TPB questionnaire. The most important consequences are changes in knowledge, attitudes, subjective norms, perceived behavioral control, and stages of intentions to have children.

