**Hypothesis**

An educational intervention based on the integration of TTM and TPB on the intention to have a child in childless couples leads to changes in knowledge, attitude, subjective norms, perceived behavioral control, and intention to have a child, which in turn changes behavior, which can lead to strategies to solve problems related to the aging population.

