## Methods/design

### Study aims

#### The main aim

The main objective of this study is to evaluate the effectiveness of an integrated theory-based educational intervention on the intentions of childless couples to have a child.

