#### Secondary aims

Evaluate changes in intentional stages.Assess the impact of the training program on factors influencing behavior (attitude, subjective norms, perceived behavioral control, and behavioral intention).To investigate the relationship between demographic characteristics of couples and the intention to have children.

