### Outcomes

#### Primary outcome

As mentioned, the most important thing in a couple's decision to have children is the intention to do so and a positive attitude towards it, so:Change the behavior of couples to the operation and maintenance phase according to the TTM after the procedureChange to a positive attitude toward having a baby.

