### Statistical analysis

The analytical method used in this study will be quantitative. The information recorded in the questionnaire will be entered into the SPSS program at each stage and data analysis will be conducted after the research process is completed. Categorical variables will be reported based on frequency, and quantitative variables will be reported as mean (SD). The ANOVA test will be used for quantitative variables that have a normal distribution, and the Friedman test will be used for quantitative variables that do not have a normal distribution. The effectiveness of the intervention will be determined using an ANOVA test and the impact of demographic variables on factors measured using a logistic regression model. Statistical analyses will be performed using IBM-SPSS 22. For all analyses, P values  < 0.05 are considered statistically significant.

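### The same outcomes are ranked differently in the abstract, hypothesis, aims and outcome sections, and effectiveness is tied to no named outcome, so a result on a secondary construct alone could be reported as effectiveness

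*Protocol article*

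**What the plan says.** The outcomes appear in seven places in the protocol article.

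- **Abstract, Methods:** "The most important consequences are changes in knowledge, attitudes, subjective norms, perceived behavioral control, and stages of intentions to have children". Five constructs, no order among them.
- **Hypothesis:** the intervention "leads to changes in knowledge, attitude, subjective norms, perceived behavioral control, and intention to have a child". Again five, unranked.
- **The main aim:** to "evaluate the effectiveness of an integrated theory-based educational intervention on the intentions of childless couples to have a child". One outcome, intention.
- **Secondary aims:** "Evaluate changes in intentional stages", and the effect on "factors influencing behavior (attitude, subjective norms, perceived behavioral control, and behavioral intention").
- **Primary outcome:** "Change the behavior of couples to the operation and maintenance phase according to the TTM", and a change to a positive attitude.
- **Secondary outcomes:** awareness of the complications of delay, sense of reproductive control, coping with society's standards, and preparedness for fertility decisions.
- **Sample size:** calculated from the mean and standard deviation of intention, and nothing else.

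The Statistical analysis section says that effectiveness will be determined by an ANOVA test, without saying on which outcome. It closes with one rule for everything: "For all analyses, P values" below "0.05 are considered statistically significant".

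**The concern.** A reader who wants to know which result decides whether the programme worked gets different answers from different sections. Attitude is primary in one place and secondary in another. Knowledge is a secondary outcome in one section and among the most important consequences in the abstract. The analysis section does not settle the matter, because its effectiveness test is attached to no outcome and its significance rule covers primary and secondary results alike.

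What is at stake is the conclusion. Suppose stage of intention and attitude show nothing, but the knowledge score differs between groups. The knowledge items are built from the material taught in the sessions (Level of knowledge), so this is the construct nearest to the teaching and the most likely to move. The text as it stands would let that result be presented as effectiveness, although it says little about intention to have a child. The abstract's Discussion expects decision-makers to use the results for national fertility policy.

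**Working it through.** **1. The ranks side by side**

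| Construct | Abstract and Hypothesis | Aims | Outcomes | Sample size |
|---|---|---|---|---|
| Intention / stage of intention | one of five | intention: main, and again secondary; stage change: secondary | stage change: primary | intention: yes |
| Attitude | one of five | secondary | primary | no |
| Knowledge | one of five | in no aim | secondary | no |
| Perceived behavioral control | one of five | secondary | secondary (sense of reproductive control) | no |
| Subjective norms | one of five | secondary | secondary only by inference (society's standards) | no |

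The conflict is complete for attitude. For stage change it is partial: the abstract speaks of stages of intention, and the TTM questionnaire measures movement in behavioral intention, so this primary overlaps the main aim even though stage change is also listed as a secondary aim.

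**2. The plan's own figure**

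The only calculation in the article is the sample size: 2.1664 × 14.82 / 2.6896 = 32.106 / 2.6896 = 11.94 (printed as 11.93), rounded to 12; with 20% attrition, 12 / 0.8 = 15 couples per group. The product reproduces. What matters here is that it uses one outcome, intention. Whether its inputs match the stated power is a separate question.

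**3. Size of the risk**

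The scenario is that neither primary (stage change, attitude) is significant but at least one of knowledge, subjective norms and perceived control is.

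Inputs: 0.05 per test from Statistical analysis; two primaries from Primary outcome; five constructs from the abstract and hypothesis. Assumptions: no true effect, one time point, two-sided normal test statistics with equal correlation r. The article gives no correlation, so r = 0, 0.5 and 0.8 are shown.

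Formula: P(only the other three) = P(any of five significant) − P(any of the two primaries significant).

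At r = 0 this can be done by hand: (1 − 0.95^5) − (1 − 0.95^2) = 0.2262 − 0.0975 = 0.1287. For r > 0 the probabilities come from numerical integration over a shared normal factor.

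| r | Any of five | Any of two primaries | Only the other three | Only the other three, favourable direction |
|---|---|---|---|---|
| 0 | 0.226 | 0.098 | 0.129 | 0.070 |
| 0.5 | 0.183 | 0.091 | 0.092 | 0.046 |
| 0.8 | 0.127 | 0.078 | 0.049 | 0.025 |

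The last column counts a test only if it is significant in favour of the intervention. At r = 0 it is (1 − 0.975^5) − (1 − 0.975^2) = 0.1189 − 0.0494 = 0.0695.

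The any-of-five column is not the size of this problem, because it includes errors on the two primaries themselves.

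**The case against.** The strongest reply is that the article does have a hierarchy. It has Primary outcome and Secondary outcomes headings, one main aim, and a sample size on one outcome. That stands: a reader might infer that there is no hierarchy at all, and the documents do not support it. The fault is that the stated hierarchies disagree.

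Second, a reader might infer that the aims demote both primaries outright. As the table shows, that holds for attitude and only partly for stage change.

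Third, a reader might take the hypothesis to mean that any one of the five constructs is enough. Its wording joins all five and continues into a causal chain towards behavior, so a knowledge-only result would not confirm it on a plain reading. If all five had to be significant, the error under no effect would be far below 0.05 (0.0008 at r = 0.5, 0.008 at r = 0.8). The route to a loose claim is therefore not the hypothesis alone. It is the unnamed outcome in Statistical analysis, together with an abstract that raises all five to the same level.

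Fourth, adjustment or gatekeeping for secondary outcomes is usually left to an analysis plan, which is not shown, and testing secondaries at 0.05 is common. That also stands, and no missing procedure is criticised here. But an analysis plan could adopt one ranking only by contradicting at least one published section.

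Finally, a true null for knowledge is unlikely in an educational trial, so the main danger is over-interpretation of a real but peripheral effect. The error rates above do not measure that.

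**Conclusion.** The outcome ranking is inconsistent in the stated text, and the analysis section leaves open which outcome decides effectiveness. A result confined to a secondary construct could therefore be reported as effectiveness.

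Under the assumptions given, the chance of that happening with no true effect is about 0.13, 0.09 and 0.05 at correlation 0, 0.5 and 0.8, and about 0.07, 0.05 and 0.02 counting only favourable results. A reader might be tempted to quote 0.18 (any of five at correlation 0.5) as the false-claim rate of this defect. That figure is not supported for this purpose, since about half of it, 0.091, is the chance of an error on the primaries. The correlations are assumptions throughout.

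The point is worth correcting because it changes what the trial may conclude. It does not show that the trial lacks a primary outcome.

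**What to change.** 1. State one ranking and use it in the abstract, Hypothesis, main aim, Secondary aims, Primary outcome and Secondary outcomes. It should agree with the main aim and the sample-size outcome, that is, intention or stage of intention.
2. In Statistical analysis, tie the effectiveness conclusion to that named primary outcome.
3. If stage change and attitude are both kept as primaries, split alpha (0.025 each) or test them in a fixed order. Two primaries at 0.05 each would carry 0.098 if independent and 0.091 at correlation 0.5. The printed sample size already assumes 99% confidence, which is stricter than 0.025, but it covers intention only.
4. Describe knowledge, subjective norms and perceived behavioral control as supportive secondary outcomes that cannot establish effectiveness on their own. They may still be tested and reported; a ban on significance statements is not needed.
5. Reword the abstract and Hypothesis so that they no longer place these constructs level with the primary outcome.

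The cost is a change of wording, with no extra participants, visits or data. The downside is that secondary results can no longer carry the effectiveness claim.

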**Discussion:**

Decision-makers will use the results of this study as a basis to design appropriate, transparent, and useful policies and interventions to improve or stop the decline of the fertility rate at the national level. Also, this study will help young couples who wish to have a child in their lifetime by providing relevant information so that they do not miss this opportunity and face the consequences of delaying having a child.

*Trial registration* This study was approved by the Iranian Registry of Clinical Trials (IRCT), Number: IRCT20220618055210N2, Date of registration: 2023-10-03

## Background

Childbearing is one of the main factors of population dynamics and plays an important role in the change in population size and structure [1, 2]. This phenomenon is a multidimensional concept with familial, social, economic, cultural, political, and religious implications [3]. One of the significant concerns, which began at the end of the nineteenth century, is the decreasing fertility rate, which has been felt throughout the world [4–6].

Iran as a developing country, has experienced a sharp decline in the fertility rate, and during the last three decades [7], the total fertility rate (TFR), has fallen from 6.3 in 1986 to 1.62 in 2018[8]. It is estimated that Iran’s population growth will reach 1% by 2025 [9] and will fall to less than 1% by 2031 [10]. This is while in the religious and cultural context of Iran, having children is a virtue and one of the main motivations for getting married and starting a family, and couples’ families expect couples to have their first child soon after marriage [11].

One of the main causes of the fertility rate decline is changing fertility patterns and the increasing average age at marriage [12]. Delayed childbearing increases the risk of unintended infertility and limits the number of children in each family [13]. However, studies have shown that couples believe that their reproductive behavior is completely under their control and are often unaware of the consequences of late conception and increasing age at first pregnancy [2, 14]. Increasing parental age is associated with increased infertility and fertility risks such as miscarriage; ectopic pregnancy; multiple pregnancies; low birth weight; gestational hypertension and diabetes; maternal mortality; stillbirth; premature births; down syndrome; and birth defects including congenital heart disease, cleft palate, esophageal atresia, schizophrenia; poor neurodevelopment; and the likelihood of childhood cancer [13, 15, 16].

Unfortunately, Iranian women are largely unaware of the potential side effects of delaying childbirth, and the issue appears to be ignored by the Iranian health system [17]. This lack of knowledge inadvertently exposes them to infertility and fertility disorders, thereby increasing the need for Assisted Reproductive Technology (ART) [18]. Despite the considerable advances in ART methods as well as the public imagination and expectations regarding the successfulness of these methods, they still cannot produce conclusive childbearing or compensate for the decline in fertility as women age [19, 20]. Even in developed countries, neither women nor men fully understand the effect of age on fertility and this lack of knowledge is more common among men who are unaware of the negative effects of age, smoking, consuming alcoholic beverages, and obesity on fertility [21, 22]. Currently, many public policies are being considered to reduce such effects [23]. Consequently, in 2013, Iran enacted the Family Support Law to address these issues. However, proper implementation requires a change in the attitude of couples [24].

Since behavioral intention is a key factor in the performance of that behavior [2], it can be concluded that one effective way to change people's behavioral intention is to educate them individually or in groups to increase knowledge about fertility and change their intention [19]. Based on research, the use of theoretical models and frameworks in the design of such educational activities can increase their effectiveness [25]. Recently, the TPB has been used as a framework to address this issue, as its effectiveness in childbearing has been demonstrated in several studies [8] and it can help to understand how couples make decisions about having a child by establishing a link between attitudes and behaviors [26, 27]. According to the TPB, three determining factors influence behavioral intention: 1) the attitude, 2) subjective norms, and 3) perceived behavioral control [25, 28].

In European countries, the intention to have a first child is influenced by attitudes towards having children and subjective norms [2]. To encourage couples to decide to have children, it is necessary to find a way to alter their attitudes and subjective norms and the three components of TPB can help achieve this goal [26]. The TPB provides important information about what influences behavioral intentions but does not adequately explain the extent and manner of desired behavior change [29]. For this purpose, the TTM model can well describe the process of change or how people move toward the desired change [30, 31]. Knowing where a person is in the stage of change is useful for designing appropriate interventions that encourage the person to make the desired changes [32]. The TTM model includes 5 constructs: stages of change, the process of change, levels of change, self-efficacy, and decision balance; the most popular of these is "stages of change", which can determine how health behaviors change [33]. This dimension has 6 steps: Pre-contemplation, Contemplation, Preparation, Action, Maintenance, and Termination [34]. The effectiveness of this theory in changing behavior has been confirmed in several fields, and an intervention study in Iran also used this theory to change childbearing behavior [26]. However, limited research has used a combination of these two models to change behavior, and based on a review, a combination of these two theories has been used to change healthy behavior in exercise, cancer screening, diet, and smoking behavior [34].

The average age of marriage in Iran is 27 [35]. About 30% of women experience their first pregnancy within 5 years of marriage, and about 4% remain childless after 10 years of marriage [17]. On the other hand, female infertility starts to increase from the age of 30, and by the age of 40, 1 in 6 women are no longer able to conceive, and after age 40, more than half of women lose their ability to conceive [21]. Therefore, the present study intends to provide them with the right information before facing the decline in fertility. The assumption is that informing couples can help them make appropriate decisions about having children so that even fewer couples will suffer mental and physical disability from infertility and its high medical costs in the future. On the other hand, it is necessary to minimize the consequences of an aging society to an appropriate level. In this study, the plan is to use the TPB theory to train people and measure people's behavior changes after an intervention based on the TTM model, because this model is very effective in accurately measuring the stages of change and the amount of change.

**Hypothesis**

An educational intervention based on the integration of TTM and TPB on the intention to have a child in childless couples leads to changes in knowledge, attitude, subjective norms, perceived behavioral control, and intention to have a child, which in turn changes behavior, which can lead to strategies to solve problems related to the aging population.

## Methods/design

### Study aims

#### The main aim

The main objective of this study is to evaluate the effectiveness of an integrated theory-based educational intervention on the intentions of childless couples to have a child.

#### Secondary aims

Evaluate changes in intentional stages.Assess the impact of the training program on factors influencing behavior (attitude, subjective norms, perceived behavioral control, and behavioral intention).To investigate the relationship between demographic characteristics of couples and the intention to have children.

### Trial design

This study is a parallel group clinical trial. The TTM and TPB are used for training and measuring outcomes. The participants are childless couples who have been married for at least 2 years and are in the pre-contemplation and contemplation stages of having children. A diagram of the research process is shown in Fig. 1. After the intervention, their attitudes, subjective norms, and perceived level of control over childbearing behavior will be compared with before the intervention, to determine whether the interventions lead couples out of the pre-contemplation stage to later stages or not. The duration of this study is approximately 2 years from the beginning of the training to the end of the follow-up (6 months after the intervention). This study was approved by the Ethics Committee (Ethics Code: IR.TUMS.FNM.REC.1402.013) of Tehran Medical University. Informed consent is completed by all participants after an explanation of the objectives of the study, the research process, and the follow-up period.

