### Inclusion criteria

Aged from 18 to 40 years old for women and up to 45 years old for men, want to participate in research, being in the pre-contemplation or contemplation stage, married for 2 years or more, no contraindications to pregnancy, have no history of infertility, use of contraceptives, have no mental disability that interferes with learning.

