#### Trans-theoretical model questionnaire (TTM)

At the beginning of the study, to find out whether the person meets the criteria to enter the study or not, the participant must fill out a questionnaire about the stages of change, and whether they are in the pre-contemplation or contemplation stage, it is included in the study. This questionnaire is designed based on the stages of the change model and includes 7 questions to determine which stage the person is in. After the intervention, each participant's level of change toward the next steps in behavioral intentions will be measured using this questionnaire according to specific steps.

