### Sample size

To provide a power of 95% with a 99% confidence interval using the following formula and considering the mean and standard deviation of intention to have based on the findings of a similar study by Moghaddam et al. [36]. The sample size was estimated at 12, and then considering 20% attrition, we plan to recruit 15 couples per group and a total of 30 couples study participants.$$n=\frac{{( {z}_{1-\frac{\alpha }{2}}+ {z}_{1-\beta } )}^{2} ({s}_{1}^{2}+ {s}_{2}^{2})}{{({\mu }_{1}- {\mu }_{2})}^{2}}=\frac{2.1664 \times 14.82}{2.6896}=\frac{32.106048}{2.6896}=11.93 \cong 12$$

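### The stage outcome has two different thresholds, and one of them, if scored as a status, is already met at baseline by participants who enter in contemplation

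*Protocol article*

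**What the plan says.** The protocol article describes the stage outcome in several places.

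- **Background** gives the order of the stages: "This dimension has 6 steps: Pre-contemplation, Contemplation, Preparation, Action, Maintenance, and Termination".
- **Trial design** says that participants will be compared with their pre-intervention state "to determine whether the interventions lead couples out of the pre-contemplation stage to later stages or not".
- **Outcomes, Primary outcome** lists, as one of two items, a change in couples' behaviour that reaches what it calls operation and maintenance on the TTM. Operation is not one of the six named stages; I read it as Action.
- **Trans-theoretical model questionnaire (TTM)** says the instrument "includes 7 questions to determine which stage the person is in". Later scoring is described person by person: the "level of change toward the next steps in behavioral intentions will be measured using this questionnaire according to specific steps". No threshold is set there.
- **Secondary aims** includes "Evaluate changes in intentional stages", although the Outcomes section treats stage change as primary.
- **Inclusion criteria** require "being in the pre-contemplation or contemplation stage".
- **Abstract, Methods** puts randomisation after a step described as "After collecting baseline data and separating participants in the pre-contemplation and contemplation stages based on the TTM".
- **Statistical analysis** names ANOVA for effectiveness and for normally distributed quantitative variables, the Friedman test for non-normal ones, and logistic regression for demographic influences. It names no method for an ordered stage.

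**The concern.** A primary outcome needs one definition of success. Here the design section and the outcome section draw the line at different stages, and the instrument section draws none. The stages between the two lines, contemplation and preparation, are plausible places for participants to be after four educational sessions, so the choice of line could decide the result. If the line is not fixed beforehand, it can be chosen after the data are seen.

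The second issue concerns only the lower line. People who enter in contemplation have already left pre-contemplation. If the Trial design sentence is scored as a follow-up status without reference to the starting stage, these people count as successes in both arms without having changed. With 15 couples per group there is little room for a loss of contrast of that kind.

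**Working it through.** **Step 1. Set the statements side by side.** Stage order is from Background; Operation is read as Action. Trial design is scored here as not being in pre-contemplation.

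| Stage at follow-up | Trial design | Primary outcome |
|---|---|---|
| Pre-contemplation | no | no |
| Contemplation | yes | no |
| Preparation | yes | no |
| Action | yes | yes |
| Maintenance | yes | yes |

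The two agree at the ends and disagree for contemplation and preparation. (Termination lies beyond both lines; the Primary outcome text does not mention it.)

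**Step 2. Apply them to the permitted starting stages.** Someone entering in pre-contemplation is one stage from the Trial design line and three from Action. Someone entering in contemplation is already past the Trial design line and two stages from Action. So no entrant meets the Primary outcome threshold at baseline, but every contemplation entrant meets the Trial design one if it is scored as a status.

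**Step 3. Dilution under the Trial design line.** Let c be the share entering in contemplation, equal in both arms. Let pC and pT be the probabilities that a pre-contemplation entrant leaves that stage in the control and intervention arms. If contemplation entrants do not regress:

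- control rate = c + (1 − c) × pC
- intervention rate = c + (1 − c) × pT
- difference = (1 − c) × (pT − pC)

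The article gives none of c, pC or pT. Taking pC = 10% and pT = 40%, a 30-point gain, purely as an assumption:

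| c | Control | Intervention | Difference |
|---|---|---|---|
| 0 | 10.0% | 40.0% | 30 points |
| 0.25 | 32.5% | 55.0% | 22.5 points |
| 0.50 | 55.0% | 70.0% | 15 points |
| 0.75 | 77.5% | 85.0% | 7.5 points |

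The factor (1 − c) does not depend on the choice of pC and pT. It also holds if contemplation entrants regress at the same rate in both arms, because that term cancels from the difference.

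**Step 4. What this could mean at the planned size.** With 15 independent units per arm and a two-sided two-proportion comparison at 0.05, power for the rows above is about 47%, 23%, 13% and 8%. With an assumed 10% versus 60%, it is about 86%, 54%, 30% and 15%. The article does not name this test, so the figures show direction and scale only.

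**Step 5. The article's own figure.** The only planning figure is the sample size. The printed arithmetic, 2.1664 × 14.82 / 2.6896 = 11.94, rounds to the stated 12 per group. It rests on the mean and standard deviation of intention, not on a stage proportion, so it cannot show which threshold was meant.

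**The case against.** The strongest reply is that the Trial design sentence is narrative. It gives no time point, threshold or statistic, and the declared outcome stands under Primary outcome. The two statements are also nested: anyone in action or maintenance has left pre-contemplation. And the phrase about leading couples out of a stage describes movement, which a person who starts and stays in contemplation has not made. The TTM section likewise speaks of change.

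Much of this stands. The statements are not mutually exclusive, and the dilution arises only under a status reading of one of them. A reader might infer that admitting contemplation entrants dilutes any effect on stage. The article does not support that: nobody meets the Primary outcome threshold at entry, and under a change measure a person who stays put scores zero. A reader might also infer that success is counted per couple, so that a rule for discordant spouses is missing. The article speaks of couples loosely, measures stage for each participant, and states no couple-level rule.

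The abstract's step of separating participants by stage could mean grouping as well as screening, and baseline handling may be set out in a fuller document. But that step defines no success criterion.

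What the reply does not remove is that the design section says what the trial is to determine in terms that classify two of the six stages differently from the primary outcome. Nothing in the article says which governs.

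**Conclusion.** The point holds in a limited form. The thresholds in Trial design and Primary outcome differ, and they give opposite answers for participants in contemplation or preparation at follow-up. The TTM section does not settle the matter. That follows from the text, given only that operation means Action.

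The dilution is conditional. It applies to the Trial design statement alone, and only if that is scored as not being in pre-contemplation. The risk difference is then multiplied by (1 − c), assuming that contemplation entrants do not regress (or do so equally in both arms). Because c is not given, the size is unknown; 22.5, 15 or 7.5 points from an assumed 30 are illustrations at 25%, 50% and 75%. The Primary outcome threshold is unaffected.

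This should be corrected before analysis, because it concerns a primary outcome and the correction is cheap.

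**What to change.** 1. State one stage outcome. Align the Trial design sentence with the Primary outcome, or limit it to participants in pre-contemplation at S0. Use the stage names from Background (Action in place of operation), and make the TTM and Secondary aims sections agree.
2. Name a single primary stage analysis: a between-arm comparison of person-level stage at 6 months as an ordinal outcome, adjusted for S0 stage and allowing for clustering within couple. Movement is then judged against each person's own starting stage, and no couple-level rule is needed.
3. Report the proportion in action or maintenance by arm descriptively, so that it does not become a second primary test.

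No new data are needed, since stage is already collected at baseline and at 6 months. The cost is revised wording and one model in place of ANOVA or Friedman for this outcome; the Friedman test compares repeated measurements and does not compare arms. The limitation is size. With 30 couples, or 24 if the planned 20% attrition occurs (12 per group × 2), some stages will be sparse. The model should be kept simple, with S0 stage as the only baseline covariate and a rule for merging sparse adjacent stages fixed before the data are seen.
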